### 231 **Exploratory objectives**

- 232 • To assess the efficacy of local nicardipine application via controlled-release polymers  
233 (NicaPlant®) on:

234 Incidence of vasospasm-related morbidity/mortality within 21 days post-aneurysm  
235 rupture or before patient discharge, defined by at least one of the following:

- 236 ○ DIND.
- 237 ○ Death caused by vasospasm, delayed ischemic neurological deficit (DIND),  
238 infarcts or complications due to anti-vasospasm therapy.
- 239 ○ The need for anti-vasospasm rescue therapy before patient discharge or within  
240 21 days post-aneurysm rupture.

- 241 • To assess the pharmacokinetic profile of NicaPlant® (local nicardipine application via  
242 polymers) in plasma and its levels in CSF (only in patients provided with an EVD at  
243 time of CSF removal for medical reasons).

- 244 • To assess the effect on clinical outcome and mortality following aSAH at week 12.

- 245 • To assess the effect on clinical outcome and mortality following aSAH at Week 52.

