### 939 ***Clinical Outcome***

940 Clinical Outcome is measured at Weeks 12 & 52 post-aneurysm rupture by modified Rankin  
941 Scale, Glasgow Outcome Scale (Extended), Montreal Cognitive Assessment tool.  
942 Additionally, mortality caused by SAH complications will be recorded.

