#### 1085 **Power & Sample size**

1086 In order to ensure that the investigation of efficacy is adequately powered, the sample size  
1087 requirements are derived for the primary endpoint of interest.

1088 The primary endpoint is the Incidence of Cerebral Angiographic Vasospasm (Moderate to  
1089 Severe) at day 8 and these rates are compared for the active and control treatment groups  
1090 using the Fishers Exact test for differences in proportions. PASS software (Version 12; NCSS  
1091 LLC, Kaysville, UT, USA) was used for all calculations.

1092 A total of 40 patients (20 in each group) is in fact sufficient to detect a clinically relevant  
1093 difference of 50% between the active treatment and control group (active: 20%, control:  
1094 70%) with a two tailed significance level of 5% and 84% power.

1095 The Incidence rates from previous published work (Barth et al.,2007) were used as an  
1096 indicator of the likely incidence rates observed in a similar population with similar  
1097 investigations (Active: 7%, Control: 73%).

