## 1098 **Populations for analysis**

1099 Three main patient analysis sets will be described. These include the Full Analysis Set (FAS),  
1100 Per protocol (PP) and Safety sets. The FAS set is considered the primary analysis set for all  
1101 primary and secondary efficacy endpoints. The PP set will also be used to analyse the  
1102 primary efficacy endpoint and will consist of those patients in the FAS set without any major  
1103 protocol deviations. These will be defined in the SAP. The Safety set is considered the  
1104 primary set for all safety evaluations.  
1105 For the purpose of evaluating PK and PD endpoints, separate Pharmacokinetic and  
1106 Pharmacodynamic analysis sets will be defined.

1107 All available data of deceased patients will be included in the analysis sets.

1108

1109

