1155 -Incidence of morbidity/mortality (DIND; death due to vasospasm, DIND, infarcts or  
1156 complications due to anti-vasospasm therapy) by patient discharge.

1157 -Need of anti-vasospasm rescue therapy by patient discharge.

1158 -Clinical outcomes at week 12 and week 52, following assessment with modified Rankin  
1159 Scale (mRS) scored 0-6 (with incidence of 'Good' outcome scores 0-2) and Glasgow  
1160 Outcome Scale (extended) (GOSE) scored 0-8 (with incidence of 'Favourable' outcome  
1161 scores 6-8), together with the Montreal Cognitive Assessment Tool (MOCA) (score 0-30  
1162 higher better) and Health related quality of life, assessed using the EQ-5D-5L and SF36. The  
1163 Length of stay in hospital and the ICU will also be assessed as measures of clinical outcome .  
1164

1165 The additional information reported as an addendum to the final report will specifically  
1166 include the final assessment for clinical outcome (mRS and GOSE), assessed at week 52,  
1167 together with any additional adverse events (specifically those that are CNS related), together  
1168 with the MOCA, EQ-5D-5L and SF36.

1169 These data can be considered binary, ordered categorical or interval in nature.

1170 All binary outcomes will be evaluated using the same methods as those for the primary  
1171 endpoint (Fishers exact test).

1172 Ordered categorical data will be analysed using the Cochran-Mantel-Haenzel (CMH) test  
1173 (with modified ridits). Ordinal logistic regression may be supplemented if other covariates of  
1174 interest are identified (e.g. age, gender, WFNS).

1175 Normally distributed Interval data will be analysed using an analysis of variance (ANOVA)  
1176 model including treatment group as fixed effect and (if possible) baseline or other  
1177 explanatory variables as covariates (e.g. age, gender, WFNS). Estimates of treatment effects  
1178 and treatment differences will use LS means and 95% confidence intervals.

1179 Non-parametric alternatives, however, will be substituted if these data are non-normally  
1180 distributed (eg: Length of stay). This may take the form of the Wilcoxon rank sum test or a  
1181 ranked based ANOVA model.

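### Exploratory endpoints: the week 12 and 52 mortality item counts only SAH-caused deaths although the objective sets no cause limit, and length of stay has no death rule, so early death can pass as a short stay

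*Protocol*

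**What the plan says.** **Mortality.** The Exploratory objectives include "To assess the effect on clinical outcome and mortality following aSAH at week 12", and the same again at Week 52. Neither limits the cause of death. The recorded items do. The visit lists for Visits 6 and 7 and the list of other exploratory endpoints name mortality due to SAH. The Clinical Outcome paragraph under Clinical Evaluations says "Additionally, mortality caused by SAH complications will be recorded". The in-hospital morbidity/mortality composite is narrower still: it counts deaths from vasospasm, DIND, infarcts or complications of anti-vasospasm therapy.

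**Length of stay.** In the statistical section, under Efficacy Endpoints, "Length of stay in hospital and the ICU will also be assessed as measures of clinical outcome". Length of stay is the named example of data that call for a non-parametric method: "distributed (eg: Length of stay). This may take the form of the Wilcoxon rank sum test or a" rank-based ANOVA. The Hospitalisation section says only that both stays are recorded. Populations for analysis adds "All available data of deceased patients will be included in the analysis sets", and Replacement of Withdrawn Patients treats patients who die as having completed the study.

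**Cognition and quality of life.** MoCA, EQ-5D-5L and SF36 are compared at weeks 12 and 52. The protocol gives no rule for death on these scales.

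**The concern.** The mortality problem is a mismatch inside the protocol. A fatal infection or an implant-related death could be judged not due to SAH and so fall outside the item that is meant to answer the mortality objective. Bacterial meningitis is itself a named primary safety outcome. Independent adjudication is described for DIND and rescue therapy only, so attributing a death to SAH would rest on site judgement.

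The length-of-stay problem is one of direction. A shorter stay reads as better. If a patient who dies early in hospital contributes the days up to death as a completed stay, that death takes one of the most favourable ranks. An arm with more early deaths can then appear to do better on a measure the protocol calls a clinical outcome. In a trial of 40 patients, an apparent reduction in ICU stay could be carried forward as supporting evidence.

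**Working it through.** **The plan's own figure.** The protocol says "A total of 40 patients (20 in each group) is in fact sufficient to detect a clinically relevant" "difference of 50% between the active treatment and control group (active: 20%, control": "70%) with a two tailed significance level of 5% and 84% power". Exact power is the sum of Bin(x; 20, 0.20) × Bin(y; 20, 0.70) over all pairs (x, y) whose two-sided Fisher p-value is at most 0.05. This gives 84.6%, so the stated 84% is reproduced. Nothing below changes it.

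**Mortality.** No arithmetic applies. The objective covers all deaths after aSAH; the visit lists, the other exploratory endpoints and the Clinical Outcome paragraph all cover only SAH-caused deaths. The second set is contained in the first, so the item cannot fully answer the objective.

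**Length of stay: direction.** Let dA and dC be the proportions dying early in hospital in the active and control arms. Suppose survivors have the same stay distribution in both arms and every death falls earlier than any survivor's discharge. The chance that a random active patient has the shorter recorded stay (ties split) is

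dA(1 − dC) + (1 − dA)(1 − dC)/2 + dA·dC/2 = 0.5 + (dA − dC)/2.

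- 25% vs 10%: 0.5 + 0.15/2 = 0.575.
- 40% vs 10%: 0.5 + 0.30/2 = 0.65.
- With death ranked worst the sign reverses: 0.425 and 0.35.

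Under these conditions the direction does not depend on the shape of the survivors' stay distribution.

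**Length of stay: size.** From the protocol: 20 per arm, Wilcoxon test, two-sided 5% (nominally 2.5% in each direction). Assumed, because the protocol gives no such figures: death rates, death days and stay distribution. Survivors have identical log-normal stays in both arms, with log-SD 0.4.

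| Deaths, active vs control | Significantly shorter stay in arm with more deaths | Mean difference in medians | Same test, death ranked worst |
|---|---|---|---|
| 10% vs 10%, random (A) | 2.4% | not tabulated | 2.3% |
| 25% vs 10%, random (A) | 12.5% | −2.2 days | 0.3% |
| 40% vs 10%, random (A) | 36.9% | −5.6 days | 0.05% |
| 5 vs 2, fixed (B) | 7.0% | −2.4 days | 0% |
| 6 vs 2, fixed (B) | 11.7% | −3.5 days | 0% |
| 8 vs 2, fixed (B) | 28.2% | −6.1 days | 0% |

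A: median stay 20 days, deaths on days 2 to 10, number of deaths random. B: median 24 days, deaths on days 3 to 14, number of deaths fixed.

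Since 25% × 20 = 5 and 10% × 20 = 2, the 12.5% and 7.0% rows describe the same death rates. A rerun shows that they differ mainly because the number of deaths is random in one and fixed in the other: under either set of stay assumptions, random counts give about 12% and fixed counts about 7%.

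With 6 vs 2 deaths, medians of 18 to 30 days and log-SD of 0.3 to 0.5, the apparent advantage runs from 2.1 to 5.2 days and the false-favourable rate from about 9% to 12%. With death ranked worst, the main 6 vs 2 case goes significantly against the arm with more deaths in 11.2% of trials.

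**The case against.** - **The protocol never says that a death is scored as a short stay.** This is correct. It says that data of the deceased are included and that those who die are completers; it does not say what value their stay receives. Being in an analysis set is compatible with ranking death worst, and a later SAP could say so. The wording also leaves the rank test open between two forms. What stands is that the statements the protocol does make lead to the raw stay unless a further rule is added, and none is given.
- **A reader might infer that cognition and quality-of-life analyses drop the dead.** The protocol does not say this. It is silent, and the SAP can properly settle the rule. Ranking death worst on MoCA would also turn a cognition scale into a composite.
- **A reader might infer that excess deaths would be hidden.** The documents do not support that. Death is mRS 6 and GOSE category 1, both assessed at weeks 12 and 52, and falls outside the good or favourable outcome on each. Fatal events are SAEs reported whatever their cause, and the DSMB reviews adverse events unblinded.
- **The sizes rest on assumed inputs.** This is also correct. The up-to-67% mortality in the background describes aSAH in general, and this trial excludes WFNS grade V and major complications during repair. With equal mortality the simulation shows no bias.

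**Conclusion.** The point holds at minor-to-moderate weight, for exploratory endpoints only.

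The mortality mismatch is on the face of the protocol and needs no assumption. For length of stay, the direction of bias is certain if early in-hospital deaths enter as recorded and one arm has more of them. Its size depends on the assumed excess: about 7 to 12% false-favourable results at 25% versus 10% deaths, about 28 to 37% at 40% versus 10%, and none beyond the nominal rate when mortality is equal.

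It would go too far to say that the plan drops the dead from cognition and quality of life, or that it conceals harm overall. The primary endpoint and its 84% power are untouched.

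**What to change.** 1. **Mortality.** In the Exploratory objectives, the Visit 6 and 7 lists, the other exploratory endpoints and the Clinical Outcome paragraph, make all-cause mortality at weeks 12 and 52 the mortality outcome reported by arm. Keep SAH-related death as a breakdown, and state who assigns the cause. Vital status should already be available from mRS and SAE reporting, so no new assessment is needed.
2. **Length of stay.** Under Efficacy Endpoints, state that in-hospital death takes the worst rank in the ICU and hospital stay comparisons. Alternatively, analyse days alive and out of ICU or hospital in a fixed window, saying how readmissions are counted. Survivors' stays can be shown descriptively. The cost is a sentence of interpretation, because the result becomes a composite of death and stay.
3. **MoCA, EQ-5D-5L and SF36.** Leave the rule to the SAP. Survivor results shown beside all-cause mortality by arm would be acceptable.

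The whole change is wording and analysis code.

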### 275 **Exploratory Outcome Endpoints**

276 The exploratory outcome endpoints are:

- 277 • Incidence of vasospasm-related morbidity/mortality within 21 days or before  
278 patient discharge, defined by at least one of the following:
  - 279 a. DIND.
  - 280 b. Death caused by vasospasm, delayed ischemic neurological deficit (DIND),  
281 infarcts or complications due to anti-vasospasm therapy.
  - 282 c. The need for anti-vasospasm rescue therapy.
- 283 • Length of Intensive Care Unit (ICU) stay
- 284 • Length of Hospital Stay
- 285 • Clinical outcome at Week 12 post-aneurysm rupture as measured by:
  - 286 a. Modified Rankin Scale (mRS) – “Good Outcome” defined as mRS of 0 to 2
  - 287 b. Glasgow Outcome Scale (Extended) (GOSE) – “favourable outcome” of 6-8,  
288 “unfavourable outcome” of 0-5
  - 289 c. Montreal Cognitive Assessment tool (MoCA) - score 0-30 higher better
  - 290 d. Health related quality of life assessed using the EQ-5D-5L and SF36.

- Long-term Clinical outcome at Week 52 post-aneurysm rupture as measured by:
  - a. Modified Rankin Scale (mRS) – “Good Outcome” defined as mRS of 0 to 2
  - b. Glasgow Outcome Scale (Extended) (GOSE) – “favourable outcome” of 6-8, “unfavourable outcome” of 0-5
  - c. Montreal Cognitive Assessment tool (MoCA) - score 0-30 higher better
  - d. Health related quality of life assessed using the EQ-5D-5L and SF36.

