### 1124 ***Data Descriptions:***

1125 Data will be summarised according to patient population (FAS/PP/Safety), dose group (10  
1126 Implant/Control), assessment (Visit 1-6 / day where appropriate) and time (where  
1127 appropriate). Data collected on visit 7 will be reported and analysed in an addendum to the  
1128 study report.

1129 Categorical variables will be summarised as proportions (with 95% Clopper-Pearson  
1130 confidence intervals) and frequencies (if appropriate) and as odds ratios (with 95% Wald  
1131 confidence intervals), where logistic regression models are used. Continuous variables will be  
1132 summarised as Least square means and 95% confidence intervals, where analysis of variance

1133 (ANOVA) models are used and then also as supporting descriptive statistics (n, mean,  
1134 median, standard deviation, minimum, and maximum). Graphical displays appropriate to  
1135 these types of data will be used to present important findings.

1136 ***Treatment Group Comparability:***

1137 Surgical details (including Clip ligation & Implantation) and measures at baseline (including:  
1138 demographics, medical history, concomitant medication, physical examination, pregnancy  
1139 test) will be summarised descriptively by treatment group (10 Implant/Control) and overall.  
1140 No formal comparisons of the treatment groups at baseline will be made.

1141 ***Efficacy Endpoints:***

1142 The primary efficacy endpoint is the incidence of cerebral angiographic vasospasm (moderate  
1143 or severe) at Day 8±1. This is considered a binary outcome and the difference between the 10  
1144 Implant and Control groups will be investigated using Fishers Exact test. Proportions in the  
1145 two groups with 95% Clopper-Pearson confidence intervals will be used to quantify the  
1146 magnitude of the difference. In case cerebral vasospasm (moderate or severe) is occurring  
1147 before day 8, this measurement will replace the assessment at day 8±1.

1148 A supporting Ordinal logistic regression model (utilising all classified categories) will also be  
1149 used to provide odds ratio estimates (+/-95% confidence intervals) for the treatment effect  
1150 and associated significance levels (p-values).

1151 Secondary endpoints include the:

1152 -Incidence of new cerebral infarcts on CT scan at day 14±1, or before patient discharge,  
1153 (compared post-treatment CT scan).

1154 Exploratory endpoints include the:

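### The exploratory mRS and GOSE analyses use an unadjusted test and leave covariates optional, although age and WFNS grade are known for every patient at entry; low severity

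*Protocol*

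**What the plan says.** Protocol section 2 (Exploratory Outcome Endpoints) lists mRS, GOSE, MoCA, quality of life and lengths of stay under "The exploratory outcome endpoints are". Section 11 (Statistical endpoints, Efficacy Endpoints) assigns a method to each type of data:

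- **Binary outcomes** (such as mRS 0-2 or GOSE 6-8): "All binary outcomes will be evaluated using the same methods as those for the primary" endpoint, that is, Fisher's exact test without covariates.
- **Ordered outcomes:** "Ordered categorical data will be analysed using the Cochran-Mantel-Haenzel (CMH) test". No stratum or covariate is named. The adjusted model is a possible addition: "with modified ridits). Ordinal logistic regression may be supplemented if other covariates of" interest turn up, with age, gender and WFNS as examples ("interest are identified (e.g. age, gender, WFNS").
- **Normally distributed interval outcomes:** an ANOVA "model including treatment group as fixed effect and (if possible) baseline or other" explanatory variables, with the same three examples.
- **Other interval outcomes:** "Non-parametric alternatives, however, will be substituted if these data are non-normally" distributed. Length of stay is the example, and the substitute is either a Wilcoxon rank sum test or a rank-based ANOVA.

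The inclusion criteria (section 4) limit age to 18-75 years and WFNS to grades III and IV. Both variables are therefore recorded for every patient, and WFNS has two levels.

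**The concern.** In a trial of 40 patients, adjusting for baseline variables that predict the outcome is one of the few cheap ways to gain precision. The protocol itself names age and WFNS as candidates, and both are complete before randomisation. Even so, it makes the unadjusted test the stated analysis for the ordered scales and attaches conditions to every use of covariates.

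Two things are at stake. One is power on the clinical outcomes. The other is that an open covariate set and an open rank method leave room for a choice made after the data are seen. The clinical scales carry interpretive weight: the Population text in section 1 cites a trial of another local calcium antagonist that reduced vasospasm without improving 90-day outcome in grade I-II patients.

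**Working it through.** **1. The plan's own figure.** Inputs from Power & Sample size: 20 per arm, 20% against 70%, two-sided 5%, Fisher's exact test. Summing the binomial probabilities of all 21 x 21 possible tables with p ≤ 0.05 gives power 0.846, against the stated 84%. The figure reproduces, and nothing below touches it. No power is stated for any clinical outcome.

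**2. Ordered outcomes.** The documents give no clinical effect size and no covariate strength, so these are assumptions: a seven-level outcome cut from a latent logistic variable, odds ratio 4, and age plus WFNS explaining a share R² of latent variance. CMH on ranks is compared with rank ANCOVA (ranks regressed on treatment, age and WFNS), 20 per arm.

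| Assumed R² | CMH | Rank ANCOVA | Change (points) |
|---|---|---|---|
| 0 | 68% | 66% | -2 |
| 0.05 | 65% | 65% | 0 |
| 0.15 | 59% | 64% | +5 |
| 0.25 | 52% | 62% | +10 |
| 0.35 | 46% | 60% | +14 |

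A repeat with 12,000 trials per setting agreed within about one point. At other assumed effects (log odds ratios 1.2 and 1.6), non-prognostic covariates cost 1 to 2 points (53.3% to 52.2%; 79.2% to 77.1%). Strongly prognostic ones gained 8 to 9 points (43.5% to 51.7%; 64.7% to 73.8%). With no effect, both tests reject in about 5% of trials.

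**3. Interval outcomes.** Power = Φ(δ/(σ√(1-R²)) × √(n/2) - 1.96), with n = 20. An unadjusted power of 50% needs δ/σ = 1.96 × √(2/20) = 0.620. At R² = 0.3: 0.620/√0.7 = 0.741; 0.741 × √10 = 2.343; Φ(2.343 - 1.96) = 65%. For R² = 0.1, 0.2 and 0.4 the results are 54%, 59% and 72%. The formula ignores the degrees of freedom spent on covariates, so it is slightly generous. The gain is lost only if the condition on covariates leads to their omission.

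**4. Type I error, nominal 5%.**

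- A fixed rule (Shapiro test, then t-test or Wilcoxon) rejects in 5.1% of null trials with normal data and 5.2% with lognormal data.
- Claiming the smaller p of t-test and Wilcoxon: 5.9% to 6.4%.
- Claiming the smaller p of CMH and one adjusted rank model: 5.7% to 7.3%.
- Claiming the best of all 8 subsets of age, gender and WFNS: 9% to 11%.

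**5. Which adjusted model.** An adjusted proportional-odds model tested by likelihood ratio (1,500 null trials per setting) rejected in 6.3%, 5.9% and 6.7% at R² of 0, 0.15 and 0.25, against 4.9% to 5.1% for CMH. The Monte Carlo standard error is √(0.05 × 0.95/1,500) = 0.6 points. At this sample size rank ANCOVA holds its level better.

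**6. Chance imbalance.** If 12 to 28 of 40 patients are grade IV (assumed 30% to 70%) and allocation is a simple 20:20 split, the hypergeometric probability that the arms differ by 4 or more grade IV patients is 30% to 34%.

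**The case against.** The strongest objection is that this belongs to the SAP. The protocol announces a detailed SAP, and covariate lists, normality criteria and the choice of rank method are commonly settled there. Their absence is no fault of the protocol. What remains is what the protocol does fix: the stated test for the ordered scales is unadjusted, and adjustment is at most a supplement.

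Second, the endpoints are exploratory, with no alpha allocated and no power claimed. That stands and sets the severity.

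Third, the gain rests on assumptions. WFNS is cut to two grades, which limits how much it can predict, and chance imbalance does not invalidate an unadjusted randomised comparison. Both points stand, so the result is given as a range that includes a loss.

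A reader might also infer that the result is allowed to choose the model. The text does not say so. CMH is the named test and regression would be added to it, not swapped for it; no wording allows the smaller p-value to be claimed, and nothing dates the choice of covariates after unblinding. The 9-11% figure describes a best-of-eight search that the protocol does not propose. The normality switch depends on distribution shape, and a fixed rule keeps the error near 5%.

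**Conclusion.** The point holds, with low severity. For mRS and GOSE the plan states an unadjusted CMH test where a fixed adjustment for two baseline variables is available at almost no cost. At an assumed odds ratio of 4 this gives up about 5 to 14 points of power for assumed R² of 0.15 to 0.35. There is no gain at 0.05, and adjustment costs 1 to 2 points if the covariates are not prognostic. For interval outcomes the shortfall is only potential, because covariates may enter the main ANOVA; it would be wrong to read every clinical outcome as tested unadjusted. Error inflation is likewise conditional: about 6-7% if CMH and one adjusted model are both run after unblinding and the smaller p-value is claimed. The primary test and its 84% power are unaffected.

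**What to change.** Before unblinding, in the protocol or SAP:

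- Name one analysis for mRS, GOSE and skewed outcomes such as length of stay: rank ANCOVA with treatment, age (continuous) and WFNS (III against IV).
- Keep unadjusted CMH or Wilcoxon as sensitivity analysis.
- Report the odds ratio from the adjusted proportional-odds model as an estimate only, without its test.
- Put the same two covariates into the ANOVA for normally distributed scales, and delete the conditional wording on covariates in both places.

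The cost is a change of wording, since both variables are already collected. The downside is a power loss of 1 to 2 points if neither variable is prognostic.
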